### Data management and flow

The Data Management and Coordinating Centre for the study is located at the Ottawa Hospital Research Institute (OHRI) in Ottawa, Ontario. The Ottawa Methods Centre, located at the OHRI, will develop, maintain and host a secure, password protected web-based study database into which study personnel with granted access will input study data.

The Data Management and Coordinating Centre for the CanROC Registry is located at St. Michael’s Hospital in Toronto, Ontario and is managed by the Applied Health Research Centre (AHRC). The CanROC Registry is a web-based secure, password-protected data entry interface and corresponding database. In most cases, the CanROC variables will be obtained from the participating local CanROC site. Where direct acquisition is not available, a request will be made for transfer from the CanROC Registry.

Data flow (Fig. 1) for the study will involve regular interactions between participating Communication Centres, the study Coordinating Centre and the CanROC Site or CanROC Coordinating Centre.

**Fig. 1 Fig1:**
[figure not shown]
Proposed data flow options

Each month during the study period, a list of potentially eligible cases will be generated by each participating Communication Centre and sent to the Study Coordinating Centre in Ottawa for classification. The Coordinating Centre will obtain a parallel list of study-eligible, confirmed cardiac arrest cases over the same time period, from the corresponding CanROC Site or the CanROC Registry. The two lists will be compared and classified into one of the four categories (eligible, ineligible, missed, overcalled). This final list of eligible cases will then be sent back to the Communication Centre for preparation. Depending on the resources available at each site, one of the following will then occur:
Study staff at each Communication Centre will locate the 9–1-1 recordings, remove all identifying information and securely transfer them to the Study Coordinating Centre in Ottawa for review. Trained study staff in Ottawa will extract the study data and enter it into the study database.Study Coordinating Centre will train local study staff to review 9–1-1 recordings, extract the study data and enter it into the study database.

The Study Coordinating Centre will adopt a pragmatic approach to accommodate possible manpower limitations, provincial regulations, privacy concerns or other issues. Where there are deviations from these processes, the revised flow will be documented.

Once the recordings have been reviewed and the required information obtained, the Study Coordinating Centre will request the CanROC variables for the eligible and missed cases.

The data will be pushed securely to the study database and will be linked via run number and call date.

Extensive steps have been taken to ensure the protection of patient privacy. At the Study Coordinating Centre, all incoming data will have been transferred securely and stripped of identifying information. No direct identifiers are included in the data being collected, information which is obtained during routine, standard care with no direct contact with research participants. De-identified electronic files will be stored securely on a network folder with access limited to essential study personnel. Paper files are stored in a locked cabinet, in a locked room.

The CanROC Site data will be entered using a secure, password-protected interface on the CanROC Registry. No direct personal health identifiers are collected in the CanROC Registry and no source documents are uploaded. The transfer of the CanROC variables to the Study Coordinating Centre will be outlined in an agreement agreed upon by all parties and will occur via a secure File Transfer Protocol (FTP).

### Data analysis

#### Overall survival to hospital discharge and community bystander CPR rates – objectives 1 and 2

Individual time series plots for each of the 5 regions will be created to visually inspect the immediate and long-term effects of the intervention, and the presence of trends, cyclical patterns, and outliers. The aggregated monthly rates in each region, expressed as percentages, will be analyzed using a simple linear segmented autoregressive model. To avoid instability due to small numerators and denominators at some sites, multiple sites within the same region will be pooled for the analysis where necessary. The model will include fixed terms for time pre-intervention, intervention, and time post-intervention. The implementation period will be censored from analysis by coding the intervention variable as missing during these months [43]. The model will be estimated using maximum likelihood estimation. Statistical significance will be obtained as the estimated beta coefficients divided by their standard errors with standard errors accounting for the autoregressive parameters. As the primary analysis will be conducted at the aggregate level, no covariates will be adjusted for in this analysis. We will assess serial autocorrelation, non-stationarity, and seasonality using the Durbin-Watson statistic, Dickey-Fuller unit root test, and visual inspection of residual plots against time. The fit of the final model will be assessed by inspecting residuals around the predicted regression lines. In case of substantial non-normality, the analysis will be conducted on the log or logit scale. The effect of the intervention will be expressed for each outcome as intercept and slope changes, where the former can be interpreted as the immediate effect of the intervention and the latter as the gradual effect of the intervention on each outcome over time. We will also evaluate the difference, at 12 months post-implementation, between the fitted post-implementation rates and the projected rates estimated using only the pre-intervention data. This represents the counterfactual effect, that is, the difference between the observed rate and the rate that would have been observed had the intervention not been implemented. We will express these differences on absolute or relative scales, with 95% confidence intervals (CI) calculated using the method of Zhang et al. [44]

To obtain pooled estimates across all five regions, two methods will be used: First, we will use a random effects meta-analytical approach to pool the five region-specific intervention effect estimates and their standard errors. Next, we will use generalized linear mixed effects regression of the site-specific data with random intercepts for the sites and random slopes for time. All analyses will be conducted using SAS version 9.4 (SAS Institute, Inc., Cary, North Carolina).

#### Successful completion of telecommunication-assisted CPR instructions and frequency of CPR instructions leading to chest compressions in rare victims not in cardiac arrest – objective 3

We will use descriptive statistics with 95% CIs to describe successes in various stages of the implementation of CPR instructions (e.g. instructions offered, provided, completed, chest compressions initiated), and the frequency with which chest compressions are (rarely) going to be provided to a victim not in cardiac arrest.

#### Frequency and impact of agonal breathing on OHCA recognition by telecommunicators – objective 4

The frequency and impact of agonal breathing (proportion of missed OHCA as a result of agonal breathing) will be reported using kappa and descriptive statistics with 95% CI. Sensitivity, specificity, negative and positive predictive values will be computed with 95% CIs for the ability of ambulance telecommunicators to recognize OHCA over the telephone. OHCA recognition rates will be compared in the before and after periods using statistical analyses described above for Objectives 1 and 2.

#### Speed with which OHCA is recognized and telecommunication-assisted CPR instructions are initiated – objective 5

Descriptive statistics with 95% CIs will be used to describe various time delays occurring during telecommunication-assisted CPR instructions (e.g. time to OHCA recognition, to initiation, and to completion of instructions). We will compare these time intervals (continuous variable) in the before and after periods using statistical analyses similar to those described above for Objectives 1 and 2.

#### Objectives 6, 7, and 8

In addition to the meta-analytic (across all sites) approach proposed for the analyses of Objectives 1 and 2, we plan to stratify our interrupted time series analyses to explore the impact of 6) the studied community/site; 7) the telecommunication system/platform used; and 8) the telecommunicators’ training background and current local training on agonal breathing on the previously stated primary and secondary outcomes (Objectives 1–5).

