## Methods/design

### Study design

We propose a multiple baseline interrupted time series (ITS) design (using month as a time unit) which compares our stated outcomes over 12 months before and 12 months after the implementation (over a 1-month transition period, with possible inter-site variability based on site size) of the theory-based educational intervention on recognition of agonal breathing. The ITS design is a robust quasi-experimental design which is ideal for our study because: 1) Withholding this potentially life-saving intervention from control groups could possibly be considered unethical by some review boards; 2) Most sites would only participate if ultimately given an opportunity to implement the intervention; and 3) It will account for heterogeneity across sites in their underlying baseline trends and changes in response to the intervention. In addition, this design will give us the ability to explore the effects of our intervention while taking into account possible seasonal variations and secular trends.

Each site will implement the educational program on agonal breathing at their earliest convenience, and enter into a 12-month evaluation period (12 months/time periods after the implementation of the educational program). The evaluation period for all sites could possibly be spread over 18 months given their respective training completion. This will leave us with 6–12 months to complete data collection and analyses.

Data for the 12-month control period preceding the implementation of the educational program (12 months/time periods) will be obtained retrospectively once a site’s evaluation period is determined. Ambulance Communication Centres are already required to keep their telecommunication recordings for at least 5 years, and CanROC will have already prospectively collected all the other required outcome measures throughout.

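### Maximum likelihood with a coefficient-over-standard-error test on 24 monthly points per region understates the standard errors: if the autoregressive term is always fitted, regional nominal 5% tests reject about 10–23% of the time

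*Protocol article*

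**What the plan says.** The Study design section sets the series length: the study "compares our stated outcomes over 12 months before and 12 months after the implementation", with month as the time unit. The Data analysis section (Objectives 1 and 2) sets the model: "The aggregated monthly rates in each region, expressed as percentages, will be analyzed using a simple linear segmented autoregressive model". It lists the terms: "The model will include fixed terms for time pre-intervention, intervention, and time post-intervention". With an intercept that makes four mean parameters. Transition months drop out: "The implementation period will be censored from analysis by coding the intervention variable as missing during these months".

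Estimation and testing are also fixed: "The model will be estimated using maximum likelihood estimation. Statistical significance will be obtained as the estimated beta coefficients divided by their standard errors". In full, the sentence on testing reads "Statistical significance will be obtained as the estimated beta coefficients divided by their standard errors with standard errors accounting for the autoregressive parameters".

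The first of two pooling methods is a random-effects meta-analysis that will "pool the five region-specific intervention effect estimates and their standard errors". The second is a mixed model on site-level data.

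The article gives no autoregressive order, residual-variance divisor, reference distribution, significance level, autocorrelation value or meta-analytic estimator.

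**The concern.** Two known small-sample faults of maximum likelihood act together here. It divides the residual sum of squares by the number of points although four mean parameters were estimated. It also pulls the autocorrelation estimate downward, because the fitted level and trends absorb part of the serial dependence. Both shrink the standard errors, so the ratio of coefficient to standard error is too large.

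This model carries survival (the primary outcome), bystander CPR and the before-after comparison of recognition. Similar methods are planned for the time intervals, and the stratified analyses reuse it. The regional standard errors also supply the weights and the precision of the meta-analysis. The design has no concurrent control group, so the validity of these intervals is a main safeguard against reporting a change that did not occur.

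**Working it through.** **The plan's own figure.** The only numerical design figure is 500 cases per month: 6000/12 = 500 (and 7000/12 = 583). It reproduces at the lower end and has no bearing on the error rate. The plan states no type I error to reproduce.

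**Inputs from the article.** Points per region: n = 12 + 12 = 24, with one transition month between them missing. Mean parameters: 4. Yearly cases from Table 1: British Columbia 2800, Alberta 2400, Ontario 1650 + 291 + 250 + 134 + 102 = 2427, Nova Scotia 585, PEI 100 (total 8312). Survival 8%, from the Background.

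**Assumptions.** AR(1) errors, true autocorrelation φ from 0 to 0.4, two-sided 5%, no true effect.

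**Monthly SD.** 100·√(0.08 × 0.92 / monthly cases) percentage points. British Columbia: 100·√(0.0736/233.3) = 1.78. PEI: 100·√(0.0736/8.33) = 9.40. These affect only the pooling weights; a region's own rejection rate does not depend on its SD.

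**Two readings of the stated test.** (a) Variance SSE/24 with a normal reference. (b) Variance SSE/(24 − 4 − 1) = SSE/19 with t on 19 df. Against a REML-type divisor of 24 − 4 = 20, reading (a) alone shrinks the standard error by √(20/24) = 0.91. The downward bias in φ does the rest.

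**Simulation.** Exact Gaussian AR(1) likelihood, 20,000 series per region and φ, with repeat runs of 6,000 sets of five regions. Under (a) the mean standard error was 0.77 of the true SD of the estimate at φ = 0 and about 0.66 at φ = 0.4. The mean estimate of φ was −0.19 when the truth was 0, and 0.09 when it was 0.4.

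Rejection of a true null (ranges span repeat runs and contrasts; rows marked * are level change only):

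| Procedure | φ = 0 | φ = 0.2 | φ = 0.4 |
|---|---|---|---|
| Region, ML, reading (a) | 15–16% | 18–19% | 22–23% |
| Region, ML, reading (b) | 9–10% | 12–13% | 15–16% |
| Region, AR term only after Durbin-Watson* | 5.2% | 9.4% | 14.4% |
| Region, REML, t on 20 df | 7% | 7–8% | 9–10% |
| Pooled, ML (a), DerSimonian-Laird, normal | 8–9% | 8–9% | 10–11% |
| Pooled, ML (b), DerSimonian-Laird, normal | 7–8% | 7–8% | 9–10% |
| Pooled, AR term only after Durbin-Watson* | 4.8% | 6.6% | 8.9% |
| Pooled, REML, Hartung-Knapp t on 4 df* | 6.4% | 6.3% | 6.9% |
| Pooled, ML (a), Hartung-Knapp t on 4 df* | 5.9% | 5.7% | 5.8% |
| Pooled, true SEs, DerSimonian-Laird, normal* | 3.7% | 3.7% | 3.5% |

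The last row shows that the pooled excess comes from the understated regional standard errors: with correct ones the same pooling is slightly conservative.

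**Checks.** Binomial counts at φ = 0 gave 15–16% regionally and 8–10% pooled. A separate state-space ML fit (300 runs) gave 15% at φ = 0 and 17–24% at φ = 0.3. A default standard-error computation (outer product of gradients) gave 7–12%, with convergence warnings, so the size also depends on how the software forms the standard error.

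**The case against.** A reader might infer that the plan's tests simply run at 15–23%. The text does not support that. Those figures need the ML variance, a normal reference and an AR(1) term that is always fitted, and the article states none of the three. A residual-df variance with a t reference fits its wording equally well and gives about 10–16%. The missing details may stand in an analysis plan that is not shown. What stands is that the article itself chooses maximum likelihood and the ratio test, and both readings exceed 5%.

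The article also plans to assess autocorrelation with the Durbin-Watson statistic. If the AR term were dropped when that test is negative, error would be nominal at φ = 0. The article specifies an autoregressive model and states no such rule; with one, regional error would still reach about 14% at φ = 0.4.

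Three wider readings also fail. The 12-month counterfactual interval uses a cited method that was not simulated. The mixed-model pooling does not use the regional standard errors. And the meta-analytic excess depends on a normal interval: Hartung-Knapp with the ML standard errors already gives just under 6%.

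The plan's statement that standard errors account for the autoregressive parameters is no answer, because the estimate plugged in is itself biased downward.

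**Conclusion.** The point holds with its conditions attached. With 24 points, four mean parameters, and maximum likelihood without correction, the regional level- and slope-change tests are anti-conservative whenever the AR term is always fitted. For AR(1), φ from 0 to 0.4 and an inferred two-sided 5% level, rejection is about 10–16% to 15–23%, depending on the variance divisor and reference distribution. The first pooling method, if DerSimonian-Laird with a normal interval, rejects about 7–11%, an excess of 2 to 6 points. The autocorrelation is entirely assumed; higher values make it worse (27–31% regionally at φ = 0.6 under the harsher reading). Nothing here shows error inflation in the mixed model or in the cited 12-month interval.

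**What to change.** In the Data analysis section for Objectives 1 and 2, replace maximum likelihood with REML, fitted by region, with a t reference and Satterthwaite or Kenward-Roger degrees of freedom. In the pooling paragraph, carry those standard errors into the meta-analysis and use a Hartung-Knapp interval for the five regions.

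This is a large but partial correction: about 7–10% regionally and 6–7% pooled. Those figures were obtained with t on 20 df; the Satterthwaite and Kenward-Roger versions were not simulated.

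One autocorrelation parameter shared by all regions brings error to about 5–6% regionally, but only if the regions truly share it. With φ of 0.6, 0.4, 0.2, 0 and 0 (British Columbia, Alberta, Ontario, Nova Scotia, PEI), shared REML rejected the level change 18% of the time in British Columbia and 9% pooled, against 11% and about 8% for region-specific REML with t. Keep it as a sensitivity analysis, or for use where the regional estimates are compatible.

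The cost is a sentence or two in each paragraph and somewhat wider intervals. It needs no new data.

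### The pooled mixed model lists no term for month-to-month or serially correlated variation, so, read as a binomial model, its intervals are too narrow if such variation exists

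*Protocol article*

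**What the plan says.** The study is an interrupted time series "using month as a time unit", comparing outcomes "over 12 months before and 12 months after the implementation". For survival to discharge (primary) and bystander CPR, the Data analysis section says that the monthly regional rates "will be analyzed using a simple linear segmented autoregressive model". Significance comes from coefficients divided by standard errors, "with standard errors accounting for the autoregressive parameters". Checks are planned on these series: "We will assess serial autocorrelation, non-stationarity, and seasonality using the Durbin-Watson statistic", together with a unit root test and residual plots.

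Two pooled analyses follow. In the first, "we will use a random effects meta-analytical approach to pool the five region-specific intervention effect estimates and their standard errors". The second is "generalized linear mixed effects regression of the site-specific data with random intercepts for the sites and random slopes for time". For this second model the article names no distribution, link, dispersion parameter, residual structure or robust standard error. It does not say which pooled result prevails if the two differ.

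**The concern.** A site intercept moves a site's whole series up or down, and a site slope tilts it along a straight line. Neither follows a run of good or bad months. In a binomial model with only these two random effects, the months within a site are independent given those effects, and their variance is purely binomial. The reference distribution then assumes both that the intervention has no effect and that there is no month-to-month variation beyond binomial noise. If the second part fails, ordinary fluctuation around the implementation date passes for a change in level or slope.

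At stake is one of only two pooled estimates of the primary outcome. Its interval could be too narrow, and it could disagree with the autoregressive analysis for reasons unrelated to the programme. The pooled estimate that looks more precise might be so only because it leaves out a variance component that the regional analysis allows for.

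**Working it through.** **The plan's own figures.** The Sample size section gives 6000–7000 cases a year, 500 cases and 50 survivors a month. 6000/12 = 500 (7000/12 = 583) and 50/500 = 10% survival, so these reproduce. The article states no type I error, power, shock size or autocorrelation for the pooled model.

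**Inputs from the article.** Ten sites, 12 + 12 months, start staggered over 6 months, and Table 1 volumes (total 8312 a year).

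**Assumptions.**
- Volumes scaled to 6500 a year; the joint Edmonton/Calgary figure of 2400 split equally.
- Survival 10%; bystander CPR 30% (the earlier multi-centre study reports 28.7%).
- Two-sided 5% test.
- AR(1) month shocks on the logit scale, SD 0.1 to 0.3. Multiplying by p(1−p), SD 0.1 is 0.9 points for survival (0.09 × 0.1) and 2.1 points for bystander CPR (0.21 × 0.1); SD 0.2 is 1.8 and 4.2 points.

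**Simulation under no effect.** Binomial-logit mixed model with dispersion 1, random site intercept and time slope, and fixed time, level change and slope change; penalised quasi-likelihood; 800 runs per row. Entries are rejection rates for level change / slope change / 12-month difference.

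| Shock SD, lag-1 correlation | Survival 10% | Bystander CPR 30% |
|---|---|---|
| none | 5.0 / 5.6 / 5.6% | 5.1 / 5.8 / 5.5% |
| 0.1, 0.4 | 7.7 / 7.2 / 7.5% | 9.5 / 10.4 / 10.0% |
| 0.2, 0 | 10.1 / 10.6 / 11.1% | 16.8 / 18.9 / 18.0% |
| 0.2, 0.4 | 14.7 / 15.2 / 16.4% | 25.0 / 22.8 / 24.1% |
| 0.3, 0.4 | 22.6 / 24.6 / 24.1% | 37.4 / 40.0 / 37.9% |
| 0.1, 0.4, shared by all sites | 10.1 / 13.1 / 12.5% | 16.6 / 20.5 / 19.1% |

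The Monte Carlo standard error is about 0.8 to 1.7 points. At SD 0.1 to 0.2 with correlation 0.4, the ratio to nominal is 7.2/5 = 1.4 up to 16.4/5 = 3.3 for survival, and 9.5/5 = 1.9 up to 25.0/5 = 5.0 for bystander CPR.

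**Hand check.** For site-specific shocks, the variance of a pooled contrast grows by roughly k = 1 + m·p(1−p)·SD²·(1+ρ)/(1−ρ). Here m is the case-weighted mean number of cases per site-month, Σn²/Σn = 109.5 with the scaled volumes. Rejection is then P(|Z| > 1.96/√k).
- Survival, SD 0.2, ρ 0: k = 1 + 109.5 × 0.09 × 0.04 = 1.39, giving 9.7%.
- Survival, SD 0.2, ρ 0.4: the last factor is 1.4/0.6 = 2.33, so k = 1.92, giving 15.7%.
- Survival, SD 0.1, ρ 0.4: k = 1.23, giving 7.7%.
- Bystander CPR, SD 0.1, ρ 0.4: k = 1 + 109.5 × 0.21 × 0.01 × 2.33 = 1.54, giving 11.4%.
- Bystander CPR, SD 0.2, ρ 0.4: k = 3.15, giving 26.9%.

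These are close to the simulated rates, slightly high for bystander CPR. The formula also shows why bystander CPR suffers more: p(1−p) is 0.21 against 0.09. With ρ = 0 and SD 0.2 the inflation is already about 2 times for survival and 3.4 to 3.8 times for bystander CPR, so overdispersion is a large part of the cause.

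**The case against.** The strongest reply is that the article gives this model one condensed sentence. Family, link and residual structure are not stated, and an article may leave residual covariance and dispersion to the analysis plan, which is not shown. That stands in part: the binomial reading is an inference. It is a natural one, since both outcomes are yes/no and the wording moves from a linear model for the regions to a generalized linear one for the pooling. A Gaussian model with an estimated residual would absorb independent overdispersion but still not autocorrelation; that case was not simulated. The article is also not silent on structure. It lists the random effects, and by the standard it sets for the regional model the list is short.

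Second, the regional section does not assert that the rates are serially correlated. It allows for that and plans to test it. This stands, so every statement of size here is conditional.

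Third, the shock sizes may be generous. At the largest site, British Columbia, 2800/12 = 233 cases a month gives a binomial SD of √(0.1 × 0.9/233) = 2.0 points, so a survival shock of 1.8 points is nearly as large as the sampling noise there. This is why the smaller shock, about 1.5 times nominal for survival, is kept as the lower end of the range.

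Fourth, the pooling method listed first already carries the regional standard errors, "standard errors accounting for the autoregressive parameters". This stands and limits the consequence.

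A reader might infer that the pooled test is known to reject a true null two to four times too often, or that all pooled inference on survival is compromised. The documents support neither. They give no shock size, there is no inflation without shocks, and the meta-analysis does not share this defect.

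**Conclusion.** The point holds in conditional form. As listed and read as a binomial model, the second pooled analysis has no term for extra-binomial or serially correlated monthly variation, although the regional analysis of the same outcomes allows for autocorrelation. If such variation exists, its intervals are too narrow. With assumed site-month shocks of logit SD 0.1 to 0.2 and lag-1 correlation about 0.4, a true null is rejected about 1.5 to 3 times too often for survival and 2 to 5 times for bystander CPR; with no shocks the model holds its level. The cause is overdispersion as well as autocorrelation, so describing it as a missing autoregressive term alone would miss part of it. This is a cheap improvement to one of two pooled analyses, not a flaw in the regional analysis.

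**What to change.** Add to the second pooling model (i) a site-by-month random effect with AR(1) correlation within site, and (ii) a calendar-month effect shared by all sites. State the distribution and link. Name a plain overdispersion term as the fallback if the model does not converge, noting that it covers extra variation but not serial correlation.

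The AR(1) site term was tried in 300 runs per scenario (Monte Carlo standard error up to about 2 points). With site-specific shocks of SD 0.1 to 0.3 and correlation 0.4 to 0.6, rejection of a true null fell to 3.7–8.0% for survival and 4.0–9.3% for bystander CPR. With shocks shared across sites (SD 0.1, correlation 0.4) it stayed at 7.3–9.7% and 11.7–14.0%, which is why the calendar-month term is needed too. The two terms together were not simulated.

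The cost is a sentence or two of analysis wording and two extra random terms, set before the data are analysed. Pooled intervals will be somewhat wider. Convergence may be difficult at the smallest sites: Table 1 gives Prince Edward Island 100/12, about 8 cases a month, and Thunder Bay 102/12, about 9, so about one survivor a month at 10%.
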